## Background

Parkinson's disease (PD) is a progressive neurological disorder characterized by both motor symptoms (such as bradykinesia and postural instability) and non-motor symptoms (such as depression and cognitive impairment)[1]. Both motor and non-motor symptoms can result in reduced physical activity[2,3].

Observations in non-parkinsonian populations suggest that participating in regular physical activity has preventive effects (e.g. cardiovascular events, diabetes mellitus, dementia)[4-6] and positive symptomatic effects (on depression[7], sleep disturbances[8], health-related quality of life)[9]. Studies in PD patients concluded that brief physical therapy interventions can improve flexibility, balance and muscle strength[10,11]. In addition, preclinical evidence in animals with experimental parkinsonism raised the possibility that physical activity may directly alter the neurodegenerative process[12,13].

A critical question remains how PD patients can be stimulated best to achieve an enduring increase in their physical activities in daily life, in order to prevent co-morbid complications and to improve symptoms.

Simply informing subjects about the health benefits of physical activity is not enough to attain a sustained behavioral change. The challenges to induce a lasting change in exercise behavior are particularly great for neurological patients. To change lifestyle, behavioral programs should focus on appropriate supervision, social support from spouses and caregivers, and the individual's preferences and needs[14-16]. Achieving an enduring behavioral change also calls for specific strategies such as goal setting, problem-solving techniques and motivational interviewing[14,16,17]. Physical activity promoting programs including such elements were effective in sedentary people[15], patients with chronic heart failure[16], and patients with COPD[18].

Stimulated by these observations, we developed the ParkFit program: a multifaceted intervention to promote physical activity in sedentary patients with PD. In addition, we developed the ParkFit trial to investigate whether this program affords increased physical activity levels that persist for two years. The trial will also search for possible health benefits and risks of increased physical activity. Here, we describe the study design and baseline characteristics of this ParkFit trial.

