#### Primary endpoint: level of physical activity

Primary endpoint is the level of physical activity, as measured with a 7-day recall, based on an interview-based physical activity questionnaire, the LAPAQ[35]. Patients are asked to list their daily amount of activity (frequency and duration), so total time spent on physical activity (in hours per day) will be calculated. A MET-value will be used to calculate the number of kilocalories spent per day per kilogram of body weight[36]. The LAPAQ is completed during a face-to-face interview (at baseline, 12 and 24 months) and at additional time points by telephone (6 and 18 months). We assume that patients will increase their level of physical activity during the first months of intervention and then maintain this level. Therefore, main endpoint is the level of physical activity during the entire follow-up period (i.e. the mean of 6, 12, 18 and 24 months).

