**Health Effects**					
*UPDRS III, motor function*	x		x		x
*Nine hole peg board test*	x		x		x
*Timed up and go test*	x		x		x
*DXA*	x				
*SCOPA-sleep*	x	x	x	x	x
*HADS*	x	x	x	x	x
*FSS*	x	x	x	x	x
*Cognitive testing battery**	x		x		x
*PD medication*	x	x	x	x	x
*Medical costs & EQ-5D*	x	x	x	x	x
*Number of falls (monthly)*	x	x	x	x	x

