#### Additional measures

Patients who increased their amount of physical activity will be compared with patients unable to achieve this, to assess specific health consequences. Disease progression (UPDRS motor section [39]; 9-hole peg board test[40]), mobility (Timed Up and Go test[41]), quality of sleep (SCOPA-sleep[42]), anxiety and depression (HADS[43]), fatigue (Fatigue Severity Scale[44]), and cognitive functioning (Table 2 for test battery) are assessed. Additionally, physical fitness is measured with the Åstrand-Ryhming test[45]. Bone mineral density (dual energy X-ray absorptiometry, DXA) is determined in a subgroup of 300 patients. PD medication and medical costs (combined with the EQ-5D[46]) are assessed, as well as the number of falls (as an index of safety). Patients are asked whether their falls occurred during exercise and about the consequences of falls (e.g. injuries). Information about other adverse events is collected systematically at each physical assessment.

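### The only systematic enquiry described for adverse events other than falls is yearly, so events in the first months of treatment are first asked about at month 12

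*Protocol article*

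**What the plan says.** The Background section of the protocol article makes safety an aim: "The trial will also search for possible health benefits and risks of increased physical activity".

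Under Additional measures, the routine for events other than falls is: "Information about other adverse events is collected systematically at each physical assessment". Adverse events have no row of their own in Table 2, so their timing has to be read from the timing of the physical assessments. Table 2 combines a visit with questionnaires at baseline, 12 and 24 months and lists questionnaires alone at 6 and 18 months. The physical tests, for example the row "UPDRS III, motor function", are marked at baseline, 12 and 24 months. The primary endpoint section agrees: the activity interview is a "face-to-face interview (at baseline, 12 and 24 months") and is done "at additional time points by telephone (6 and 18 months").

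Falls are handled separately. Table 2 has the row "Number of falls (monthly"), and Additional measures adds: "Patients are asked whether their falls occurred during exercise and about the consequences of falls (e.g. injuries").

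On when activity should change, the primary endpoint section says: "We assume that patients will increase their level of physical activity during the first months of intervention and then maintain this level".

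**The concern.** The article expects the exposure of interest, more physical activity, to change early. Its systematic enquiry about non-fall events does not begin until a year into treatment. The baseline enquiry comes before the intervention, so only two enquiries, at 12 and 24 months, can pick up events that follow it.

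Two things are at stake. First, minor and transient events (a strain or an overuse complaint, say) are easily forgotten or misdated over a year, and the earliest ones have the longest to fade. Second, a patient who leaves before month 12 may never be asked. Both reduce the number of events available for a safety comparison that the article sets itself. The patients are already contacted at 6 and 18 months, so the long window is not forced by the visit schedule.

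**Working it through.** The plan states no figure to reproduce here; the check is schedule arithmetic plus a range for drop-out.

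**Inputs**
- Physical assessments at 0, 12 and 24 months (Table 2; primary endpoint section).
- All scheduled assessment contacts at 0, 6, 12, 18 and 24 months (Table 2).
- 586 patients enrolled (Inclusion procedure).
- Expected drop-out 10% (Sample size calculation). Its timing is not given, so any split is an assumption.

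**Step 1: longest recall window.** This is the largest gap between successive enquiries.
- Physical assessments: max(12 − 0, 24 − 12) = 12 months.
- All scheduled contacts: max(6 − 0, 12 − 6, 18 − 12, 24 − 18) = 6 months.

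**Step 2: delay for early events.** An event in month *m* of the first year waits 12 − *m* months.
- *m* = 1: 12 − 1 = 11 months. *m* = 3: 12 − 3 = 9 months.
- With an enquiry at month 6: 6 − 1 = 5 and 6 − 3 = 3 months.

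**Step 3: patients who might never be asked after baseline.** Expected drop-outs: 0.10 × 586 = 58.6. If a share *s* of them leaves before month 12 and is not assessed afterwards, the number is 58.6 × *s*:

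| Share leaving before month 12 (assumed) | Patients with no enquiry after baseline |
|---|---|
| 25% | 14.7, about 15 |
| 50% | 29.3, about 29 |
| 75% | 44.0, about 44 |
| 100% | 58.6, about 59 |

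A constant drop-out hazard over 24 months gives 1 − 0.9^0.5 = 0.0513, and 0.0513 × 586 is about 30 patients. Under the same hazard, those leaving before month 6 number (1 − 0.9^0.25) × 586, about 15.

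**Step 4: effect on the comparison between arms.** Let *p*F and *p*S be the true event proportions in ParkFit and ParkSafe, and *c* the fraction of events captured.
- If *c* is the same in both arms, the observed difference is *c*(*p*F − *p*S): smaller than the truth, with the ratio unchanged.
- If ParkFit has proportionally more of its events early, and early events are captured less well, *c* is lower in ParkFit and the ratio shrinks as well.

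The article gives no value for *c* in either arm, so the first effect can be stated in direction only and the second only as a possibility.

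**The case against.** Several objections have weight.

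- **Other reporting routes.** A reader might infer that nothing is recorded between visits. The article does not say so. Spontaneous and serious-event reporting is commonly left to a full protocol, which is not shown. This stands; the point is confined to systematic enquiry, which mainly concerns non-serious events.
- **Falls are well covered.** The Discussion singles out falls as the safety issue, and they are recorded monthly with questions on injuries. This stands; fall injuries are not part of the gap.
- **Indirect traces.** Medication and medical costs are collected every six months, therapists register each session, and ParkFit patients are encouraged to have a sports medical screening. Some events may show up this way, but none of these is described as adverse-event collection, so they soften the gap without closing it.
- **Bias against the control arm.** A reader might infer that ParkFit will look safer than it is relative to ParkSafe. Both arms have the same schedule and blinded assessors, and the article supports only an early rise in activity, not an early cluster of events. A differential under-count is not shown.
- **Loss through drop-out.** A reader might infer that early drop-outs are certainly lost. The article does not say whether people who stop are still assessed at 12 and 24 months.
- **Blinding.** Adding the questions to the telephone interview looks easy, but an answer that reveals the programme could influence the same interviewer at later primary-endpoint interviews, even if it is given after the activity questions. This stands and decides where the questions should go.

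**Conclusion.** The point holds as a cheap improvement to a stated schedule, not as an error or an internal contradiction. For adverse events other than falls, the article describes one systematic enquiry, and its first use after treatment starts is at month 12. The longest recall window is 12 months where existing contacts would allow 6, and events in months 1 to 3 wait 9 to 11 months.

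The likely result is an under-count of non-serious, non-fall events in both arms, heaviest for early events; its size cannot be derived from the article. The figure of about 15 to 59 of 586 patients without any enquiry after baseline rests on three things: the expected 10% drop-out, an assumed 25% to 100% of it falling before month 12, and no assessment after drop-out. If drop-outs are still assessed, that part falls away and only the long recall remains. The primary endpoint and the power are not affected.

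**What to change.** Amend the adverse-event sentence under Additional measures, and add a row to Table 2, so that the same standard questions are asked at 6, 12, 18 and 24 months and at withdrawal. At 6 and 18 months, put them in the questionnaires that Table 2 already schedules, or attach them to the monthly falls record; keep them out of the telephone interview for the primary endpoint. Have the added answers received and coded by staff who do not assess outcomes.

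The cost is a few more items on existing forms and a short enquiry at withdrawal. No treatment, sample size or analysis of the primary endpoint changes. Selection ran from September 2008 to January 2010, so for patients already past month 6 the added enquiry covers only their remaining follow-up. Capture will then be uneven over time, and the safety report should state, by arm, how many patients were asked at each time point.

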#### Blinding

To avoid bias due to more positive expectations of patients towards the outcomes of the ParkFit Program, patients were initially informed about the fact that there are two intervention groups, each with a beneficial intervention. To ensure blinding during assessments, patients are assessed by trained assessors who are unaware of group allocation. Patients are explicitly asked to not share their experiences with the program during the assessments.

#### Sample size calculation

Based on the following power considerations, we aimed to include a total of 700 patients. In a small observational study on physical activity in PD, patients scored 45% less on the LAPAQ compared to controls (unpublished data). The coefficient of variation was 110%. Based on a difference of 15% (with coefficient of variation of 110%) between both treatment arms, the study will have at least 80% power (when the correlation between baseline and follow-up measurements is at least 0.50 and when the correlation between the various follow-up measurements is at most 0.85). This is also the power when the correlations are at least 0.60 and at most 0.95, respectively. The power is based on two-sided 95% confidence intervals. We assumed that patients would take part in exercise groups with on average eight participants and that the corresponding ICC would be 0.1. Based on a previous trial of physical therapy for PD involving the national ParkinsonNet networks[21], we expect a drop-out rate of 10%.

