## Results

### Inclusion procedure

Selection of patients ran from September 2008 to January 2010. A total number of 4479 patients received a screening questionnaire; 587 (13.1%) did not respond, 439 (9.8%) were excluded because there was doubt about the diagnosis (Figure 2). After invitation for participation, 1766 patients were excluded based on our exclusion criteria, and 1101 eligible patients were excluded because they were not willing to participate. Finally, 586 patients signed informed consent. The number of enrolled patients is less than the power calculation required. However, the power remains over 80% because only 60% of patients participates in exercise groups with an average group size of only three, whereas our power calculation assumed that all patients would participate in exercise in groups of eight patients.

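### The stated power of at least 80% for a 15% between-arm difference does not follow from the protocol's own inputs, either at 700 patients or at the 586 enrolled

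*Protocol article*

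**What the plan says.** The Sample size calculation section first reports an unpublished observational study in which patients' LAPAQ scores were 45% below those of controls, with a coefficient of variation (CV) of 110%. It then states the target and the power together: "Based on a difference of 15% (with coefficient of variation of 110%) between both treatment arms, the study will have at least 80% power". Two conditions are attached. The first concerns the "correlation between baseline and follow-up measurements is at least 0.50 and when the correlation between the various follow-up measurements is at most 0.85". The second gives an alternative pair: "This is also the power when the correlations are at least 0.60 and at most 0.95, respectively". The section also assumes exercise groups of eight on average, an ICC of 0.1, two-sided 95% confidence intervals and 10% drop-out. On size, "we aimed to include a total of 700 patients".

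The Inclusion procedure section reports the shortfall ("Finally, 586 patients signed informed consent") and answers it: "However, the power remains over 80% because only 60% of patients participates in exercise groups with an average group size of only three". It adds that the original calculation had put every patient in a group of eight.

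Two other sections fix the analysis. The primary endpoint section defines the main endpoint as the mean of the 6-, 12-, 18- and 24-month values. The Statistical analyses section adjusts for baseline LAPAQ and names no transformation.

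**The concern.** A 15% difference against a CV of 110% is a small standardised effect, about 0.14 SD. The plan then inflates the variance for clustering and loses a tenth of the sample. Averaging four highly correlated follow-ups and adjusting for baseline recovers only part of this. It is not obvious that 700 patients would give 80% power, and still less that 586 would.

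The figure concerns the primary endpoint, and the article uses it to reassure readers about the shortfall. A reader told that power exceeds 80% will take the risk of missing a true 15% effect to be below 20%. If the real risk is much larger, the article misdescribes which effects the trial can reliably detect.

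**Working it through.** **Inputs from the article.** N = 700 planned and 586 enrolled; difference 15%; CV 110%; baseline to follow-up correlation b and between-follow-up correlation r of 0.50/0.85 or 0.60/0.95; four follow-ups averaged; baseline adjusted; two-sided 5%; ICC 0.1; groups of eight for everyone (plan) or groups of three for 60% (as enrolled); drop-out 10%.

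**Assumed.** 1:1 allocation; drop-outs contribute no data; correlations sit at the stated bounds, which is where the 80% is claimed.

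**Step 1, standardised difference.** d = 0.15/1.10 = 0.1364.

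**Step 2, variance of the baseline-adjusted mean of four follow-ups, in units of SD².** V = (1 + 3r)/4 − b².
- 0.50/0.85: 0.8875 − 0.25 = 0.6375
- 0.60/0.95: 0.9625 − 0.36 = 0.6025

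The two are close, which agrees with the article treating the pairs as about equivalent. This suggests that the variance model is the one the authors used.

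**Step 3, design effect.** DE = 1 + (m − 1) × ICC.
- Plan: 1 + 7 × 0.1 = 1.7
- As enrolled: 0.6 × 1.2 + 0.4 × 1.0 = 1.12

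**Step 4, evaluable patients.** 700 × 0.9 = 630, or 315 per arm. 586 × 0.9 = 527.4, or 263.7 per arm.

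**Step 5, power on the untransformed scale.** SE = √(2 × V × DE / n per arm); power = Φ(d/SE − 1.96).
- 700, first pair: SE = √(2 × 0.6375 × 1.7/315) = 0.0830; d/SE = 1.644; power 37.6%. Second pair: 39.4%.
- 586, first pair: SE = √(2 × 0.6375 × 1.12/263.7) = 0.0736; d/SE = 1.853; power 45.7%. Second pair: 47.9%.

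The stated 80% is not reproduced.

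**Step 6, difference detectable with 80% power (raw scale).** 2.80 × SE × 1.10 gives 25.6% and 24.9% at 700 (the two pairs), and 22.7% and 22.0% at 586.

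**Step 7, attempts to recover 80%.**

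| Reading (two-sided) | 700 | 586 |
|---|---|---|
| Raw, stated clustering and drop-out | 38-39% | 46-48% |
| Raw, drop-out ignored | 41-43% | 50-52% |
| Raw, clustering and drop-out both ignored | 62-64% | 54-57% |
| Log scale, ratio 1.15 or 0.85, stated clustering and drop-out | 47-62% | 57-72% |
| Log scale, ratio 0.85, clustering ignored, drop-out kept | 82-84% | 75-77% |
| 15 points of the control level, stated clustering and drop-out | 85-87% | 92-93% |

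The log-scale rows use SD = √ln(1 + 1.1²) = 0.8905, so d = ln(1.15)/0.8905 = 0.157 or −ln(0.85)/0.8905 = 0.183. At 700 the log scale passes 80% once clustering alone is dropped, but only for a 15% decrease, whereas the programme aims at an increase. The last row takes patients at 55% of the control level, so 15 points is 15/55 = 27% of the patients' mean and d = 0.273/1.10 = 0.248.

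**Step 8, the relative argument.** Effective sample after drop-out: 630/1.7 = 371 as planned, 527.4/1.12 = 471 as enrolled. Fewer and smaller groups more than offset the lost patients.

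**The case against.** The best defence concerns the base of the percentage. The 15% comes just after the 45% deficit relative to controls, the only reference level the section gives. If the authors meant closing a third of that deficit, power exceeds 80% at both sample sizes and both statements are true. The reading is plausible but not established: the sentence ties the 15% and the CV to a difference between the treatment arms. If the control-level meaning was intended, the target between arms is about 27%, and the sentence still needs correcting.

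The second defence is the scale. A CV of 110% on a score that cannot be negative implies skew, and the article does not say on which scale power was computed. This stands as a limit on the size of the shortfall. A reader might infer that a true 15% effect would be missed about half the time or more. That holds on the raw scale; on the log scale at 586 the miss rate is about 28-43%. Even so, no log-scale variant tried reaches 80% once the stated clustering is applied.

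Two further inferences go beyond the text. A reader might suppose that recruitment was stopped at 586 on the strength of this figure. The article reports the recruitment period, the number enrolled and a comment on power; it describes no such decision. A reader might also conclude that a null result will be taken as evidence against a 15% effect. That is possible but not stated, and the analysis section promises 95% confidence intervals throughout, which would show the effects still compatible with the data.

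**Conclusion.** The concern holds in this form: the claims of at least 80% power at 700 and over 80% at 586 are wrong as written for a 15% between-arm difference with a CV of 110%. On the raw scale the stated inputs give 38-39% and 46-48%, and no two-sided raw-scale variant tried exceeds 64%. On an unstated log scale they give 47-62% and 57-72%. The comparison with the plan in the Inclusion procedure section is correct: the enrolled sample is no less informative than the planned one. It does not support the absolute figure.

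The exact values rest on 1:1 allocation, correlations at the stated bounds and no data from drop-outs. Correlations more favourable than the bounds would raise power, but the article claims 80% at the bounds. Endpoint, model and significance level are unaffected.

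**What to change.** In the Sample size calculation and Inclusion procedure sections, state what the 15% is a percentage of and on which scale power was computed. Then replace the 80% claim with one of the following:
- the power for a 15% between-arm difference, about 46-48% at 586 on the raw scale (38-39% for the planned 700); or
- the difference detectable with 80% power, about 22-23% at 586 on the raw scale (25-26% for the planned 700).

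If 15 points of the healthy-control level was meant, say so and give the equivalent of about 27% between arms, with the matching power. Keep the explanation that smaller and fewer groups offset the smaller sample, as a statement relative to the plan.

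The cost is rewording two sections and, unless the control-level meaning is confirmed, a less favourable stated figure. Enrolment and the planned analysis do not change.

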#### Randomization

A minimization algorithm is used to randomize patients, with the factors region, Hoehn & Yahr stage, age, gender and current level of physical activity.

#### Statistical analyses

All participants who really started with their program, will be included in the primary analysis. The results after 6, 12, 18 and 24 months will be evaluated using a linear mixed model with random nested factors 'patient' and 'exercise group'. Fixed factors will be treatment arm, LAPAQ score at baseline, month, month*treatment (interaction), and the factors region, H&Y stage, age, gender and bone density assessment. In an additional analysis, the influence of H&Y stage, age, gender and level of previous sports activities on the success of the treatment will be evaluated by including the interaction terms between treatment and each of these variables in the model. Multiple imputation analyses will be used to evaluate the impact of missing values on the outcome. Throughout, 95% confidence intervals will be calculated.

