### The Intervention

After baseline assessment, patients were randomly assigned to the ParkFit or ParkSafe Program. In both groups, patients receive high quality physical therapy: both interventions are delivered exclusively by experienced therapists who participate in the Dutch ParkinsonNet[21,22]. Patients in both treatment arms are offered an equal maximum number of treatment sessions (i.e. 35 sessions of 30 minutes a year; Table 1). Therapists contact patients at least every six months to investigate if there are new aims.

**Table 1 T1:** The ParkFit and the ParkSafe program

	ParkFit	ParkSafe
**Intensity** **Year 1**	Maximum of 19 physical therapy sessions based on problems and disabilities as perceived by each individual patient; the systematic way of tailoring goals is described in the evidence-based guideline for physical therapy in PD	Maximum of 35 physical therapy sessions based on problems and disabilities as perceived by each individual patient; the systematic way of tailoring goals is described in the evidence-based guideline for physical therapy in PD
	16 coaching sessions to identify and focus on individual beliefs and aims to promote a physically active lifestyle	
**Intensity** **Year 2**	Maximum of 23 physical therapy sessions based on problems and disabilities as perceived by each individual patient	Maximum of 35 physical therapy sessions based on problems and disabilities as perceived by each individual patient
	12 coaching sessions to identify and focus on individual beliefs and aims to promote a physically active lifestyle	
**Specific Elements**	ParkFit Brochure: • *Education about benefits of physical therapy* • *Identifying aims of physical therapy* • *Education about the benefits of physical activity* • *Identifying barriers to engage physical activity* • *Setting goals* • *Recruiting social support* • *Sign a health contract to support patients in initiating and maintaining* *physical activities* • *A logbook to describe and monitor the specific goals*	ParkSafe Brochure: • *Education about benefits of physical therapy* • *Identifying aims of physical therapy* • *Education about the importance of safety when performing* *daily activities*

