##### 4) Ambulatory Activity Monitor with visual feedback

Patients receive a personal ambulatory monitor with automated visual feedback showing the amount of actually delivered daily physical activity, recorded by a triaxial accelerometer[27,28]. Additionally, a personalized website shows the activity history[27]. Previous work showed that feedback from pedometers increases physical activity levels in COPD patients[29], sedentary workers[30] and patients with diabetes mellitus[31].

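### The primary analysis keeps only patients who began their assigned programme, a post-randomisation selection that can bias the comparison by an unknown amount

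*Protocol article*

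**What the plan says.** The protocol article names one population for the primary analysis, under Statistical analyses: "All participants who really started with their program, will be included in the primary analysis".

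Under The Intervention it places allocation earlier: "After baseline assessment, patients were randomly assigned to the ParkFit or ParkSafe Program". Starting a programme is therefore an event after randomisation.

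Under Blinding, masking is described for assessors only: "patients are assessed by trained assessors who are unaware of group allocation". On the patients' side the section says that "patients were initially informed about the fact that there are two intervention groups, each with a beneficial intervention", and adds: "Patients are explicitly asked to not share their experiences with the program during the assessments".

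The arms differ visibly. Under ParkFit Program: "Patients receive a personal ambulatory monitor with automated visual feedback". ParkFit also has a signed health contract, a logbook and coaching sessions. Table 1 lists none of these for ParkSafe. Both arms have the same yearly maximum of 35 sessions, guideline-based physical therapy and the same therapists.

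The endpoint is self-reported: "Primary endpoint is the level of physical activity, as measured with a 7-day recall", averaged over 6, 12, 18 and 24 months. On missing data, Statistical analyses says: "Multiple imputation analyses will be used to evaluate the impact of missing values on the outcome".

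**The concern.** Randomisation makes the two arms comparable as allocated. It does not make those who go on to start comparable. If the decision to start depends on the programme drawn and also on something that predicts later activity, the starters in the two arms differ for reasons other than treatment.

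Both links are plausible here. The extra ParkFit elements ask more of a patient, and willingness to take up an activity programme is probably related to how active a patient will be. Table 3 gives indirect support: eligible patients who declined the trial reported 40.1 min/week, against 59.2 in participants. That table concerns refusal of the trial and not failure to start a programme, so it shows plausibility and nothing more.

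At stake is the trial's main result. A selection bias of this kind does not shrink as the sample grows. The confidence interval would not reflect it.

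**Working it through.** **1. The plan's own figure.** There is none to reproduce. The article neither reports nor forecasts how many randomised patients did not start. The 10% under Sample size calculation is expected drop-out, with no split into never-started and stopped later. All non-start rates below are assumptions.

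**2. Shift in one arm's mean.** Let p be the share not starting and d the fraction by which non-starters fall below the full-arm mean, set to 1. Solving p(1 − d) + (1 − p)m = 1 for the starters' mean m gives

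m = (1 − p(1 − d))/(1 − p) = 1 + pd/(1 − p).

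With d = 0.50:
- p = 5%: 0.975/0.95 = 1.026
- p = 1%: 0.995/0.99 = 1.005
- p = 10%: 0.950/0.90 = 1.056
- p = 2%: 0.990/0.98 = 1.010

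**3. Shift in the contrast, compared with the planned 15% difference.**
- 5% v 1%: 2.63% − 0.51% = 2.1%; 2.1/15 = 14%
- 10% v 2%: 5.56% − 1.02% = 4.5%; 4.5/15 = 30%
- Equal rates and equal d in both arms: 0

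**4. A smaller deficit, borrowed from Table 3.** d = (59.2 − 40.1)/59.2 = 0.32. The same pairs of rates give 1.4% and 2.9%, or 9% and 20% of the planned difference.

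**5. Effect of baseline adjustment.** The model includes baseline LAPAQ. At the planned baseline-to-follow-up correlation of 0.50, and assuming equal SDs at baseline and follow-up, the slope on baseline is 0.50. If the non-starters' whole deficit is already present at baseline, adjustment removes half: 0.5 × 2.13% = 1.1% and 0.5 × 4.54% = 2.3%. If the deficit arises from motivation that baseline activity does not show, it removes none. The other covariates may remove a little more.

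**6. Exclusions in one arm only.** Express the deficit as k SDs, with the planned coefficient of variation of 110%, so the shift is b = p/(1 − p) × k × 1.10. For the type I error, assume 586/2 = 293 per arm, a variance factor of (1 + 3 × 0.85)/4 − 0.50² = 0.6375, and a design effect of 1 + 0.6 × (3 − 1) × 0.1 = 1.12 (60% of patients in groups of three, ICC 0.1). Then

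SE = 1.10 × √(0.6375 × 1.12) × √(1/293 + 1/(293(1 − p)))

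type I error = Φ(−1.96 + b/SE) + Φ(−1.96 − b/SE).

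| p | k | b, % of mean | share of 15% | type I error |
|---|---|---|---|---|
| 2% | 0.25 | 0.6 | 4% | 0.051 |
| 2% | 0.50 | 1.1 | 7% | 0.052 |
| 5% | 0.25 | 1.4 | 10% | 0.054 |
| 5% | 0.50 | 2.9 | 19% | 0.066 |
| 10% | 0.25 | 3.1 | 20% | 0.067 |
| 10% | 0.50 | 6.1 | 41% | 0.121 |

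A deficit of a full SD is left out: 1 − 1.10 = −0.10 would be negative activity time. The table sets an unadjusted shift against an adjusted SE, so its error rates are on the high side.

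**The case against.** The strongest reply is that the rule removes only patients who never began. On its wording, starters stay in whatever their later adherence, so this is not a completers or per-protocol analysis. The 1101 eligible patients who declined had left before randomisation, so those randomised had already agreed to take part. Telling patients that both programmes are beneficial should limit differing expectations, and some will fail to start through illness or logistics. All this stands, and it suggests that the numbers may be small. It does not show that they are, or that they are equal between arms.

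Second, the illustration uses chosen rates and raw means. That also stands, and is why the figures are given as conditional. In addition, part of any lower activity in ParkFit non-starters would come from not receiving the programme. That part separates the effect in starters from the effect of assignment and is not bias. Comparing ParkFit starters with ParkSafe starters still estimates neither effect cleanly if different kinds of patients start in each arm.

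Third, the article is a condensed account. A definition of starting, or sensitivity sets, may be in a fuller plan, and their absence here is no finding. The primary population, however, is stated outright. Baseline covariates adjust for only part of the selection, and imputation is described for missing values, not for patients left out of the population.

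A reader might go further on three points that the document does not support:
- That the bias favours ParkFit. This is plausible, but without non-starter counts or outcomes the direction is not shown.
- That ParkSafe is ordinary care, so that uptake must differ sharply. The article describes specialist, guideline-based therapy matched for intensity.
- That the power statement wrongly counts non-starters. The 586 are patients who consented, and planning already allowed for 10% drop-out.

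**Conclusion.** The point holds as a fault in a stated rule. The sole named primary population is conditioned on an event after randomisation, in a trial where patients are not described as masked. The comparison can be biased as a result. The document does not show that it is biased, or in which direction.

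Under the assumed non-start rates and a 50% deficit, the unadjusted shift is 2.1% to 4.5% of the mean, or 14% to 30% of the planned difference. Adjustment could leave about half of that or all of it. The shift is near zero if few patients fail to start, or if non-starters are similar in number and kind in both arms.

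That patients know their programme when they decide whether to start is an inference from the different materials and from the request to keep silent at assessments. It is a firm inference, but the article does not say so outright.

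**What to change.** Define the primary analysis as all randomised patients in the arm assigned, whether or not they started. Collect LAPAQ from non-starters at the existing visits (12 and 24 months) and telephone calls (6 and 18 months). Report the number of non-starters by arm. Keep the started set as a sensitivity analysis, with starting defined in the same way for both arms.

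The means are largely in place. Consent precedes the first assessment and randomisation follows baseline, so each randomised patient should have consent and a baseline LAPAQ. Follow-up LAPAQ is an interview, not a product of therapy sessions. The exercise-group term is no obstacle: only 60% of patients take part in groups, so the model must already handle patients outside them.

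The cost is a change of wording, follow-up of a few more patients and a small dilution of the estimated effect.
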